#### Cost measurement

For this study we have developed a cost interview especially designed for this group, based on existing questionnaires, such as the de Trimbos/iMTA questionnaire for Costs associated with Psychiatric Illness (TIC-P) [64]. Since PDs are known to interfere with all life aspects, this economic evaluation will be performed from a societal perspective, which implies that all relevant costs and outcomes are considered. Health costs covered intervention, healthcare, social work, emergency department, community health service, informal and alternative care. Costs outside the health care consist of comprised losses in productivity of (unpaid)work, study, and domestic activities up to two years, traveling costs, out-of-pocket costs (e.g., alcohol, tobacco, drugs, impulsive spending), and judicial costs. Costs are measured at baseline before random assignment to treatments, and every assessment for 2 years, using a 4-month recall period.

Total costs will be estimated using a bottom-up (or micro-costing) approach, where information on each element of service used is multiplied by an appropriate unit cost and summed to provide an overall total cost [65]. The valuation of healthcare, patient and family costs will be based on the updated Dutch manuals for cost analysis in healthcare research [66]. In brief, the manual recommends standardized cost prices for health care and shadow prices for informal care (meaning a standard cost price based on general hourly wages). Costs of transport will be calculated as the mean distance per destination multiplied by standard cost prices. Costs of medication will be calculated using prices based on Daily Defined Dosage (DDD) taken from the healthcare institute of the Netherlands^1^ indicating the mean medication usage per adult a day inclusive claw back (by the government-imposed discount for patients, paid by the pharmacy). Productivity losses will be calculated by means of the friction cost method, based on a mean added value of the Dutch working population. The friction costs method considers production losses confined to the period needed (usually 90 days) to replace a sick employee. In case of uncertainty, we will use a conservative estimation (i.e., the lowest cost price). Cost prices will be expressed in 2021 euros. If necessary, existing cost-prices will be updated to 2021 using the consumer price index (CPI). Interrater agreement of the cost interview will be assessed by blinded double coding.

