### Cost-Effectiveness and Cost-Utility Analyses

A baseline analysis will be performed to examine the comparability of groups at baseline for both costs and outcomes. We aim to use the multiple imputation method to handle missing values at item level using the individual mean score [67]. However, we will monitor recent developments in the rapidly advancing field of cost-effectives studies to decide on the most fitting technique when time is due. If necessary, methods are applied to control for differences in baseline [68]. The ICER will be determined based on incremental costs and effects of group-ST compared to TAU. The cost-effectiveness ratio will be stated in terms of costs per outcome rate, the cost-utility ratio will focus on the net cost per QALY gained. The ICER will be calculated as follows. ICER = (Ci – Cc) / (Ei – Ec), where Ci is the annual total cost of the GST, Cc is the annual total cost of TAU (resp. IST), Ei is the effect at 2-years follow-up for GST and Ec is the effect at 2-years follow-up for TAU (resp. IST). The three arms will be mutually compared, with a primary interest in the GST-TAU and the GST-IST comparisons. However, the IST-TAU difference will also be tested. The robustness of the ICER will be checked by non-parametric bootstrapping. Bootstrap simulations will also be conducted to quantify the uncertainty around the ICER, yielding information about the joint distribution of cost and effect differences. The bootstrapped cost-effectiveness ratios will be subsequently plotted in a cost-effectiveness plane, in which the vertical line reflects the difference in costs and the horizontal line reflects the difference in effectiveness. The choice of treatment depends on the maximum amount of money that society is prepared to pay for a gain in effectiveness, which is called the ceiling ratio. Therefore, the bootstrapped ICERs will also be depicted in a cost-effectiveness acceptability curve showing the probability that group-ST is cost-effective using a range of ceiling ratios.

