Additionally, to demonstrate the robustness of our base-case findings a multi-way sensitivity analysis will be performed. In the sensitivity analysis uncertain factors of assumptions in the base case analysis are recalculated to assess whether the assumptions have influenced the incremental cost-effectiveness ratio (ICER), for example by varying cost-prices and volumes between minimum and maximum [69]. For the primary research question, GST is compared to TAU. For the secondary research question, GST is compared to IST. In addition, IST will be compared to TAU.

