## Discussion

In this article the study design of a multicenter RCT into the (cost-)effectiveness of GST relative to IST and TAU for Cluster-C PDs is described. This study design will contribute to the urgent need to create treatment guidelines for individuals with Cluster-C PD and will broaden our understanding of which aspects help Cluster-C PD patients to recover and live a fulfilling life.

The main objective of this study is to assess the evidence of GST for Cluster-C PDs over IST and TAU. Group-treatment has potentially unique therapeutic advantages such as peer-support, vicarious learning, and a safe environment to practice new behaviors. Additionally, GST is already a popular treatment in clinical practice in the Netherlands and many other countries due to (assumed) advantages such as being able to treat more patients in a shorter period of time, offering a solution to the long waitlists for PD-treatment. If GST is indeed found superior to IST or TAU, this would greatly reduce pressure on the Dutch mental healthcare system. The fact that clear guidelines and protocols for GST already exist facilitates training and implementation.

This trial includes a comprehensive economic evaluation where the additional costs and additional outcomes of GST compared to IST and TAU are estimated. The gold standard for assessing the cost-effectiveness of a new treatment is comparing it to TAU. For policy makers, the comparison of GST to TAU is pivotal in the decision-making process of implementing a new treatment in clinical practice. In this specific case, a direct comparison of GST to IST is also important. First, only a direct comparison will tell us to what degree GST is cost-effective compared to IST. Admittedly, the direct delivery costs per client of GST are estimated to be 50% of that of IST. However, we don’t know how other (healthcare) costs compare between GST and IST, and how the clinical effects compare. Therefore, a direct investigation of the comparative cost-effectiveness of GST and IST is needed.

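### Pricing uncertain cost items at the lowest price is conservative for total cost but not for a comparison between arms, and can bias the base-case ICER for or against GST

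*Protocol article*

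**What the plan says.** The Cost measurement section of the protocol article builds total cost bottom-up, "where information on each element of service used is multiplied by an appropriate unit cost and summed to provide an overall total cost". Most prices have a named source. Healthcare, patient and family costs follow the Dutch costing manuals, and according to the article "the manual recommends standardized cost prices for health care and shadow prices for informal care". Transport has standard prices, medication is priced per defined daily dose, and lost productivity uses a mean value for the Dutch workforce. For whatever remains uncertain the rule is: "In case of uncertainty, we will use a conservative estimation (i.e., the lowest cost price".

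The section on cost-effectiveness and cost-utility analyses then defines "ICER = (Ci – Cc) / (Ei – Ec", applied to GST against TAU and GST against IST, with IST against TAU as a further comparison. Bootstrapping supplies the cost-effectiveness plane and the acceptability curve. Finally, "to demonstrate the robustness of our base-case findings a multi-way sensitivity analysis will be performed", "for example by varying cost-prices and volumes between minimum and maximum".

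**The concern.** A lowest-price rule suits a cost-of-illness estimate, where the aim is not to overstate a burden. An ICER uses a difference. A low price on an item that GST uses more than the comparator makes GST look cheaper. The same low price on an item that GST uses less hides part of the GST saving. One rule applied to all items and all three comparisons therefore cannot be relied on to be cautious about GST.

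At stake is the headline economic result. Bootstrapping as described quantifies uncertainty around an ICER that already contains the chosen prices, so the plane and the acceptability curve inherit them. A reader told that the prices are conservative would probably take the result as a cautious one for the new treatment, which the rule does not ensure.

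**Working it through.** The article attaches no figure to this rule, so there is nothing to reproduce. The check is algebra followed by an illustration.

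**Identity.** With unit price p and between-arm volume difference ΔQ for item k, the bottom-up costing gives

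ΔC = Σ pₖ ΔQₖ, and ICER = ΔC / ΔE.

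If the lowest price lies a fraction uₖ below the central price (uₖ = 0 for items with a standard price),

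ΔC(low) = Σ (1 − uₖ) pₖ ΔQₖ, so ΔC(low) − ΔC = − Σ uₖ pₖ ΔQₖ.

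Two things follow.

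- Each affected item's contribution moves towards zero, whichever arm uses more of it.
- The net difference moves against GST if GST saves on the uncertain items taken together, and in favour of GST if GST costs more on them. The net is certain to shrink only if all items differ in the same direction, or if all prices are lowered by the same fraction.

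**Illustration.** All inputs are assumed, because the article gives no price spreads, no item-level differences and no expected QALY difference. Amounts are euro per patient, GST minus comparator; u is varied from 20% to 40%.

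| Items at central price | Price lowered | Formula | Central | u = 20% | u = 30% | u = 40% |
|---|---|---|---|---|---|---|
| A: −1,000 and −2,000 | both | −3,000(1 − u) | −3,000 | −2,400 | −2,100 | −1,800 |
| B: intervention +1,500, other −2,000 | other only | −500 + 2,000u | −500 | −100 | +100 | +300 |
| B: same | intervention only | −500 − 1,500u | −500 | −800 | −950 | −1,100 |
| C: intervention +2,000, other −1,500 | other only | 500 + 1,500u | +500 | +800 | +950 | +1,100 |
| C: same | intervention only | 500 − 2,000u | +500 | +100 | −100 | −300 |

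With an assumed gain of 0.05 QALY for GST, dividing the u = 30% column by 0.05 gives these ICERs in euro per QALY:

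- A: −60,000 becomes −42,000.
- B: −10,000 becomes +2,000 (other only) or −19,000 (intervention only).
- C: +10,000 becomes +19,000 (other only) or −2,000 (intervention only).

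In the two rows where the sign changes, it does so at u = 500 / 2,000 = 25%. If both prices in B fall by the same 30%, the net is −500 × 0.7 = −350, which is plain shrinkage.

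**The sensitivity analysis.** It varies prices from minimum to maximum. For an item already priced at the minimum, the price can move only upward from the base case. The analysis can therefore show what the rule did, but it does not bracket the base-case price and leaves the headline ICER where it was.

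**Which direction applies here.** For GST against TAU the article gives nothing from which to derive it. For GST against IST it says that "the direct delivery costs per client of GST are estimated to be 50% of that of IST". If IST delivery costs D, the saving is D − 0.5D = 0.5D. Were the delivery price uncertain and lowered by 30%, the saving would be 0.5D × 0.7 = 0.35D, which works against GST.

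**The case against.** The strongest reply has four parts.

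- **Scope.** Most cost categories have a standard or mean price, so the rule covers a remainder that the article does not itemise. This stands. A reader might infer that the whole economic result rests on low prices; the article does not support that. The societal perspective does include categories such as judicial costs, impulsive spending and alternative care, some of which may lack a standard price, but that is an inference.
- **Disclosure and sensitivity analysis.** The rule is stated in advance, defined in the same sentence, and followed by an analysis meant to test base-case assumptions. This stands as mitigation: the effect should become visible. It does not alter the base case, the plane or the acceptability curve.
- **Bias is not shown.** It arises only where the lowest price lies below the true price on items whose use differs between arms. This stands: the rule can bias the ICER, and the article does not show that it will. Two stronger readings also fail. One is that cost differences always shrink, which is true item by item but not for the net. The other is that the ICER is pulled towards zero by some stated percentage, which would rest entirely on assumed shares and spreads.
- **Therapist time.** It is tempting to conclude that a low therapist price will understate the saving of GST over IST. Nothing in the article says that therapist time has an uncertain price. If it had, the low price would work against GST, so on that item the label would fit.

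The article may also leave the definition of uncertainty to a fuller economic plan. That would settle which items are affected, but not whether lowest is the right base-case choice for them.

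**Conclusion.** The point holds as a minor correction to a rule that the article states explicitly. Choosing the lowest price is conservative for total cost and carries no such guarantee for an incremental comparison. The base-case ICER and acceptability curve can be moved for or against GST, and only through items without a standard price. Direction and size cannot be determined from the article; the euro figures in the illustration rest on assumed inputs and show only that shrinkage, growth and reversal are all possible. The clinical primary outcome is unaffected.

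**What to change.** Replace the sentence in Cost measurement with one saying that, where no standard price exists, a central (mean or reference) price is used in the base case, identically in all three arms. Reserve the lowest and highest prices for the multi-way sensitivity analysis already planned, so that it brackets the base case on these items. Drop the word conservative.

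The cost is one sentence and the choice of a mid-price for each affected item. No new data are needed, and the change is best made before the economic analysis begins.

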### Cost-Effectiveness and Cost-Utility Analyses

A baseline analysis will be performed to examine the comparability of groups at baseline for both costs and outcomes. We aim to use the multiple imputation method to handle missing values at item level using the individual mean score [67]. However, we will monitor recent developments in the rapidly advancing field of cost-effectives studies to decide on the most fitting technique when time is due. If necessary, methods are applied to control for differences in baseline [68]. The ICER will be determined based on incremental costs and effects of group-ST compared to TAU. The cost-effectiveness ratio will be stated in terms of costs per outcome rate, the cost-utility ratio will focus on the net cost per QALY gained. The ICER will be calculated as follows. ICER = (Ci – Cc) / (Ei – Ec), where Ci is the annual total cost of the GST, Cc is the annual total cost of TAU (resp. IST), Ei is the effect at 2-years follow-up for GST and Ec is the effect at 2-years follow-up for TAU (resp. IST). The three arms will be mutually compared, with a primary interest in the GST-TAU and the GST-IST comparisons. However, the IST-TAU difference will also be tested. The robustness of the ICER will be checked by non-parametric bootstrapping. Bootstrap simulations will also be conducted to quantify the uncertainty around the ICER, yielding information about the joint distribution of cost and effect differences. The bootstrapped cost-effectiveness ratios will be subsequently plotted in a cost-effectiveness plane, in which the vertical line reflects the difference in costs and the horizontal line reflects the difference in effectiveness. The choice of treatment depends on the maximum amount of money that society is prepared to pay for a gain in effectiveness, which is called the ceiling ratio. Therefore, the bootstrapped ICERs will also be depicted in a cost-effectiveness acceptability curve showing the probability that group-ST is cost-effective using a range of ceiling ratios.

Additionally, to demonstrate the robustness of our base-case findings a multi-way sensitivity analysis will be performed. In the sensitivity analysis uncertain factors of assumptions in the base case analysis are recalculated to assess whether the assumptions have influenced the incremental cost-effectiveness ratio (ICER), for example by varying cost-prices and volumes between minimum and maximum [69]. For the primary research question, GST is compared to TAU. For the secondary research question, GST is compared to IST. In addition, IST will be compared to TAU.

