### Economic Evaluation

The economic evaluation will involve a combination of cost-effectiveness analysis (CEA) and cost-utility analysis (CUA). In a CEA, effects are presented in clinical outcomes (here the primary outcome is Cluster-C PD-severity decrease). The outcome for the CUA is Quality Adjusted Life Year’s (QALY’s), based on the EQ-5D-5L utility scores [46], and the MHQoL-7D [45] for a full description see above) primarily on Dutch utilities [63]. In the CUA, the Incremental cost-effectiveness ratio (ICER) will be expressed as incremental costs per QALY.

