Another point of attention for multicenter studies is to organize and coordinate all participating sites in a clear manner. Maintaining the quality of the study protocol over 10 sites is a demanding task which requires considerable work and effort. The two junior researchers are the central figures of the study and keep in close contact with the local research assistants and coordinators of all sites. They oversee the daily coordination of the study, prepare the meetings, monitor the progress of the study and its legal, ethical and ICT aspects. Monthly meetings are held with all site coordinators to discuss the implementation of the study and to address potential difficulties. In addition, every six months the study board (site coordinators, experience experts, project leaders, the statistician and economical expert) gather to discuss developing and setting up new components to the study protocol. Finally, we (i.e., project leaders and junior researchers, independent of the sponsor) plan on auditing every site once during the inclusion period. After that, auditing will be conducted using a risk-based approach at sites who show higher rates of dropout, lower inclusions, less accuracy in assessments etc.

As previously stated, this trial consists of an extensive economic evaluation. To express the effects of the intervention we have chosen to include a cost-effectiveness and a cost-utility analysis to explore both PD-specific improvements as QALY’s. Moreover, we have chosen to incorporate two measurements to explore quality of life: the commonly used EQ-5D and the relatively new MHQoL-7D. While the EQ-5D is dominated by physical (somatic-medical) aspects of quality of life, the MHQoL-7D focusses more on mental aspects of quality of life (e.g., mood, self-image, future perspectives etc.) making it especially relevant for this population. Incorporating both questionnaires will give us an interesting opportunity to compare these measures for their suitability for a mental health population. For the economic evaluation we have chosen a time horizon of two years covering the one-year treatment and a follow-up period of one year. Although ideally one would want to choose a time horizon to cover all long-term costs and consequences (i.e., up to a lifetime), this relatively lengthy period gives the opportunity to explore the most essential period of change.

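### The ICER definition sets annual costs against effects at two years, which conflicts with the protocol's own two-year horizon for the economic evaluation

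*Protocol article*

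**What the plan says.** The section Cost-Effectiveness and Cost-Utility Analyses gives one formula, ICER = (Ci – Cc) / (Ei – Ec), for both the cost-effectiveness analysis (CEA) and the cost-utility analysis (CUA). The terms are defined in sequence, costs first: "Ci is the annual total cost of the GST, Cc is the annual total cost of TAU (resp. IST), Ei is the effect at" two-year follow-up. The effect side in full is "Ei is the effect at 2-years follow-up for GST and Ec is the effect at 2-years follow-up for TAU", again with individual schema therapy (IST) as the alternative comparator.

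Three other places bear on the time base:

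- Discussion: "For the economic evaluation we have chosen a time horizon of two years covering the one-year treatment and a follow-up period of one year".
- Cost measurement: costs are taken at baseline and at each assessment over two years, with a recall period of four months.
- Economic Evaluation: the CEA effect is the decrease in Cluster-C PD severity. For the CUA, "In the CUA, the Incremental cost-effectiveness ratio (ICER) will be expressed as incremental costs per QALY".

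The ratio then feeds the bootstrap, the cost-effectiveness plane, the acceptability curve over a range of ceiling ratios, and the sensitivity analysis.

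**The concern.** A cost-effectiveness ratio has meaning only if its costs are those incurred to obtain its effects over the same horizon. Here the numerator is worded per year and the denominator refers to two years. The article neither sums the annual costs nor puts the effects on an annual basis.

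Cost-effectiveness against TAU and against IST is part of the trial's first two main questions, and the Discussion treats the comparison with TAU as decisive for policy makers. The bootstrap, plane, curve and sensitivity analyses all take the same cost and effect terms as input, so none of them would reveal the mismatch. If annual is read as year 1, the omission may also differ by arm. Group schema therapy (GST) and IST are completed within a year, whereas the section on drop-out and follow-up acknowledges that TAU may still be running during the follow-up period.

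**Working it through.** The article reports no cost difference, effect difference or ICER, so there is no figure to reproduce. The check is algebraic, followed by an illustration.

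**Notation.** dC1 and dC2 are the incremental costs in years 1 and 2; dE is the incremental effect over the two-year horizon.

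- Horizon-consistent ICER = (dC1 + dC2) / dE
- ICER as written = dC_annual / dE
- Factor = as written / consistent = dC_annual / (dC1 + dC2)

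**Readings of annual.**

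1. Two-year total divided by 2: factor = [(dC1 + dC2)/2] / (dC1 + dC2) = 0.50, whatever the cost profile.
2. Year 1 only: factor = dC1 / (dC1 + dC2). This is 0.50 if the difference is spread evenly, 0.75 if three quarters of it falls in year 1, and 1.00 if all of it does. If the difference reverses between the years, the factor can exceed 1 (1.25 when dC1 is 125% of the two-year difference) or be negative (−0.50 when dC1 is −50% of it).
3. Year 2 only: factor = dC2 / (dC1 + dC2), the complement of reading 2.

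**Illustration (assumed figures, none from the article).** dC1 = EUR 3,000, dC2 = EUR 1,000, dE = 0.10 QALY accumulated over two years.

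| Cost term | Calculation | EUR per QALY | Factor |
|---|---|---|---|
| Two-year total | 4,000 / 0.10 | 40,000 | 1.00 |
| Two-year mean | 2,000 / 0.10 | 20,000 | 0.50 |
| Year 1 only | 3,000 / 0.10 | 30,000 | 0.75 |
| Year 2 only | 1,000 / 0.10 | 10,000 | 0.25 |

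**Effect on the acceptability curve under reading 1.** At ceiling ratio L, an arm that costs more and achieves more is accepted when dC/2 < L × dE, that is, when dC < 2L × dE. A ceiling of 20,000 therefore acts as 40,000, and one of 50,000 as 100,000. For an arm that costs less and achieves less, the same doubling works against it: its savings per unit of effect lost are understated by half. Halving does not change the sign of the cost difference, so bootstrap points stay in their quadrant and a dominant result remains dominant.

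**Can a two-year total be built from the planned data?** Four months is 52.18 / 3 = 17.4 weeks. The assessment schedule has no visit between week 51 and two years (taken as week 104), a gap of 53 weeks. Direct coverage of that gap is 17.4 / 53 = 0.33, so about two thirds of year 2 is not directly costed.

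**The case against.** The strongest reply is that annual is a drafting slip: the two-year horizon and two years of cost collection show what is intended, and a condensed article may leave costing detail to the full plan. The intent is plausible. But the article does not leave the terms open. It defines each one, and the definition conflicts with the stated horizon, with nothing to correct it.

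Three stronger readings are tempting, and the document does not support them.

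- **Every ratio is halved.** A reader might infer a general factor of two. It needs both the two-year-mean reading of annual and a denominator of cumulative two-year QALYs. Under a single-year reading the factor follows the cost profile.
- **The CUA uses an end-point utility instead of QALYs.** The word at might suggest this. But the article names QALYs as the CUA outcome and speaks of net cost per QALY gained, and QALYs accumulate over time. The natural reading is QALYs accrued up to two years; the wording merely leaves this unstated. Nor can this reading be combined with the factor of two. Assume a utility gain rising linearly to 0.08 by week 34 (0.65 year) and then held to two years. It accumulates 0.08 × 0.65/2 + 0.08 × 1.35 = 0.134 QALY. With the assumed EUR 4,000, the consistent ratio is 4,000 / 0.134 = 29,850, whereas annual cost over the end-point gain is 2,000 / 0.08 = 25,000. The factor is then 0.84, not 0.50.
- **The error always favours the costlier, more effective arm.** That holds for such an arm under halving, but not for a cheaper, less effective one, nor in general under a single-year reading. The Discussion puts direct GST delivery costs at half those of IST, so GST could turn out cheaper, and even dominant, against IST.

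It also stands that the CEA effect, a decrease in severity, is properly a change up to the two-year assessment. There, only the cost term is at fault.

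**Conclusion.** The point holds as a conflict in the definition of the cost terms, which are wrong as written for a two-year evaluation. The factor is exactly 0.50 if annual means the two-year mean and QALYs are cumulative over two years. It is dC1 / (dC1 + dC2) if only year 1 is costed, a reading that could drop the cost of TAU continuing into year 2 while still counting its two-year effect. No single size or direction can be claimed, because the article does not say which reading applies and gives no cost data; the euro figures above are assumptions. Dominance survives simple halving. Comparison with ceiling ratios, and hence the acceptability curve, does not. The clinical primary outcome and its analysis are unaffected.

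**What to change.** Put all terms on one window, baseline to two years:

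- **Ci and Cc:** mean total cost per patient from baseline to two years, with a stated rule for extrapolating the four-month recall over the part of year 2 that no assessment covers.
- **Ei and Ec for the CUA:** QALYs accumulated from baseline to two years. This is a clarification of what the text already implies.
- **Ei and Ec for the CEA:** decrease in PD severity from baseline to the two-year assessment.
- Use these same definitions in the bootstrap, the plane and the acceptability curve.

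The cost is a reworded definition plus one extrapolation rule. No additional data collection is required, but the extrapolation is an assumption and belongs among the factors varied in the planned sensitivity analysis. The wording should be settled before the cost data are analysed, so that the cost window is not chosen with results in view.
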